## Methods

### Study Design

This study will examine individuals’ psychological, behavioral, and physiological responses to e-cigarette cues in VR among young adults aged 18 to 21 years. We focus on this age range because the transition into early adulthood often brings increased exposure to vaping-related social contexts (eg, college gatherings) [27], and this pilot allows us to first test the paradigm in adults before adapting it for adolescent populations. A between-subjects design is used to compare current e-cigarette users and nonusers, with a within-subject, counterbalanced component to assess 2 cue conditions (with and without social pressure). This mixed-design approach enables testing of cue effects and group differences while controlling for individual variability.

Prior VR nicotine cue reactivity studies have reported medium-to-large effects for the response difference between user and nonuser groups [17,28]. Based on the relevant research and using G*Power 3.1 (Heinrich Heine University Düsseldorf) for a 2 (group: vapers vs nonvapers)×2 (cue condition: social pressure vs no social pressure) mixed design, we powered the study for the group × cue condition interaction (group×cue condition) assuming a medium effect (*f*=0.25; partial η-squared ≈ 0.06; power=0.80). We assumed a within-participant correlation of *r*=0.50 between cue conditions and a nonsphericity correction of *ε*=1.0 (sphericity is not applicable with 2 within-subject levels). This yields a minimum required sample of 34 (n=17 per group). To ensure robustness and account for potential data loss (eg, eye-tracking dropout and physiological artifacts), we plan to recruit 40 participants in total (n=20 vapers and n=20 nonvapers).

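### The sample-size paragraph treats f=0.25 and partial η² ≈ 0.06 as one effect, but with r=0.50 the effect powered at N=34 is an interaction partial η² of about 0.20

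*Protocol article*

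**What the plan says.** Study Design names the test: "we powered the study for the group × cue condition interaction". The calculation was done "using G*Power 3.1 (Heinrich Heine University Düsseldorf"), for a medium effect of f=0.25 that is also given as "partial η-squared ≈ 0.06; power=0.80". Two further inputs follow: "We assumed a within-participant correlation of *r*=0.50 between cue conditions" and "a nonsphericity correction of *ε*=1.0". The result is stated as "This yields a minimum required sample of 34 (n=17 per group"), and to allow for data loss "we plan to recruit 40 participants in total (n=20 vapers and n=20 nonvapers").

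The paragraph gives neither alpha nor the G*Power effect-size option. Under Study Population and Study Flow, the article adds that 40 participants are enough to detect group effects of medium size. Under Primary Analyses, the planned test is a 2 × 2 mixed ANOVA with group between and cue condition within participants.

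**The concern.** The sentence offers f=0.25 and partial η² ≈ 0.06 as two names for one effect. That holds for a one-way between-subjects ANOVA. In a repeated-measures test, the default G*Power f is scaled by the SD of a single scene, and the correlation enters separately through the noncentrality. The partial η² that the mixed ANOVA reports for the interaction uses the within-subject error, which already reflects the correlation. The two measures therefore differ, and the sample size rests on only one of them.

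At stake is what the study can be said to detect. A reader who takes 0.06 at face value will believe that the trial has 80% power for an interaction of that size in the ANOVA output. A later study that reuses the 0.06 and 34 pairing would carry the mismatch forward.

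**Working it through.** **Inputs.** From Study Design: f=0.25, r=0.50, ε=1.0, target power 0.80, m=2 scenes, two equal groups, N=34 minimum, N=40 planned. Alpha is an assumption: the smallest balanced N is 52 at 0.01, 42 at 0.025, 34 at 0.05 and 28 at 0.10, so of these only 0.05 returns the stated figure.

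**Step 1: reproduce N=34.** Default G*Power noncentrality for the within-between interaction:

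λ = f² · N · m/(1−r), with df 1 and N−2.

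- N=32: λ = 0.0625 · 32 · 4 = 8.0, power 0.781
- N=34: λ = 0.0625 · 34 · 4 = 8.5, power 0.807
- N=40: λ = 0.0625 · 40 · 4 = 10.0, power 0.869

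So 34 is the smallest balanced N that reaches 0.80. A simulation of 50,000 data sets with 17 per group gave 0.808.

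**Step 2: express that effect on the scale of the test.** With two scenes, the interaction F-test is the square of a two-sample t-test on each participant's difference between scenes. In single-scene SD units the cell deviations are ±0.25, so the mean difference is ±0.5 in the two groups and the groups differ by 4f = 1.0. The SD of a difference score is √(2(1−r)) = √(2 · 0.5) = 1.0. Hence d = 1.0/1.0 = 1.0, and λ = d² · N/4 = 34/4 = 8.5, which agrees with Step 1.

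Partial η² of that test:

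- λ/(λ+N) = 8.5/42.5 = 0.20
- λ/(λ+df₂) = 8.5/40.5 = 0.21

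**Step 3: where 0.06 comes from.** f²/(1+f²) = 0.0625/1.0625 = 0.0588. This omits the factor m/(1−r) = 2/0.5 = 4 that Step 1 uses. With the factor, 0.25/1.25 = 0.20.

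**Step 4: power if the interaction's partial η² is 0.06.** η²/(1−η²) = 0.06/0.94 = 0.0638. The range comes from multiplying by N or by N−2.

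| N | λ | Power |
|---|---|---|
| 34 | 2.04 to 2.17 | 0.28 to 0.30 |
| 40 | 2.43 to 2.55 | 0.33 to 0.34 |

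80% power needs N = 126 to 128, or 128 to 130 with 0.0588 in place of 0.06.

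**Step 5: what the planned sizes detect with 80% power, given r=0.50.**

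| Evaluable N | λ needed | Partial η² | d = √(4λ/N) |
|---|---|---|---|
| 34 | 8.35 | 0.20 to 0.21 | 0.99 |
| 40 | 8.27 | 0.17 to 0.18 | 0.91 |

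**The case against.** A reader might infer that the stated 80% power is simply wrong. The document does not support that. N=34 and 80% follow exactly from the stated f, r and ε, so the calculation is internally sound and the fault lies in the conversion printed beside f. The figure of about 30% applies only if 0.06, read as the ANOVA's own partial η², was the effect the authors meant, and Study Design does not settle this.

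A reader might also infer that the assumed effect is large and that calling it medium is false. This depends on the scale. As cell deviations of 0.25 single-scene SDs, f=0.25 is medium by convention; as a difference in change scores it is a full SD. The article needs to name the scale, but the word is not false on the scale of f.

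Nor does the document say that a null interaction will be taken as evidence against a medium effect. The Primary Aim hypothesises group differences across both scenes and stronger responses under social pressure in both groups, and states no interaction hypothesis. The study is described as a pilot. The risk of misreading is an inference.

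Finally, r=0.50 is an openly stated assumption and not an error. Other values move power both ways: at f=0.25 and N=34, r=0.3 gives 0.67 and r=0.7 gives 0.95.

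All of these objections stand. None removes the mismatch, because no reading makes every number in the sentence true of the interaction test. If f was meant, 0.06 is wrong; if 0.06 was meant, 34 is too small.

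**Conclusion.** The point holds as a mislabelled effect size in the sample-size justification. With r=0.50, f=0.25 and partial η² ≈ 0.06 are different effects for this interaction. The one powered at N=34 has a partial η² of 0.20 to 0.21, more than three times the printed value. At a partial η² of 0.06, the chance of a significant interaction with the planned 40 is about one in three. These figures rest on alpha 0.05, r=0.50, equal groups and the default G*Power definition, which is the one that reproduces 34. The conclusion does not extend to a claim that the calculation from f is wrong or that enrolment must change.

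**What to change.** Keep N=40 and revise the sample-size paragraph under Study Design:

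- State alpha and the G*Power effect-size definition.
- Replace the partial η² of 0.06 with about 0.20, and say that medium refers to f on the single-scene SD scale.
- Add that, given r=0.50, 80% power is reached at a partial η² of about 0.17 to 0.18 (d about 0.91 on difference scores) with 40 evaluable participants, and about 0.20 to 0.21 (d about 0.99) with 34.
- Add that power at a partial η² of 0.06 is about one in three with 40 participants (28–30% with 34).
- If 0.06 was the intended effect, say plainly that the study does not have 80% power for it.
- Bring the sentence on medium group effects under Study Population and Study Flow into line with the restated figure.

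The cost is wording only. Enrolment, procedures and analysis are unchanged; the stated sensitivity of the study becomes less favourable.

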### Study Population and Study Flow

This study will recruit young adults aged 18 to 21 years living in or around New Haven, Connecticut. Recruitment efforts will focus on two distinct groups: (1) individuals who currently use nicotine-containing e-cigarettes, defined as use on 10 days or more within the past 30 days (*vapers*), and (2) individuals who report never having used nicotine-containing vapes (*nonvapers*). Participants who use nicotine in non–e-cigarette forms (eg, cigarettes and nicotine pouches) will not be excluded but will be assessed at baseline so that such exposure can be accounted for analytically. This design allows the comparison of psychophysiological cue reactivity between vapers and nonvapers, as well as the exploration of predictors of future initiation risk among nonvapers.

Eligibility will require participants to be fluent in English and able to provide informed consent. Exclusion criteria include self-reported photosensitive epilepsy, significant visual, hearing, or mobility impairment, current or recent (past 30 days) use of cannabis-containing e-cigarettes, current use of other illicit substances (eg, 3,4-methylenedioxymethamphetamine or ecstasy, and methamphetamine), nonmedical misuse of prescription drugs, or reliance on eyeglasses that are incompatible with VR eye-tracking hardware. These exclusions help reduce noise in psychophysiological responses that may arise from nonnicotine substances, ensuring clearer differentiation between the study groups. A total sample of 40 participants will be enrolled, which is sufficient for detecting medium group effects in VR cue-reactivity studies while accounting for potential data loss.

The study flow is shown in Figure 1. Eligible participants will complete a single laboratory session lasting approximately 1 hour. After providing informed consent and completing baseline questionnaires, participants will be fitted with a VR headset and biometric sensors. They will complete 3 VR scenes: a neutral baseline, a vaping cue scene without social pressure, and a vaping cue scene with social pressure in a counterbalanced order. Physiological data will be recorded continuously, and brief self-report measures (craving, presence, and social presence) will follow each cue scene. Participants will rate the system’s usability after finishing all the VR sessions. The session will conclude with a short semistructured interview, debriefing, and compensation.

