### Assessments

At the start of the laboratory visit, participants will complete the informed consent procedure and then part 1 of the assessment questionnaire. Part 1 contains self-report measures on vape perception, substance use intentions and behaviors, and psychosocial assessments (Table 1).

**Table 1. T1:** Baseline and trait-level measures assessing vaping-related behaviors, substance use, and psychosocial characteristics among participants.

Measures	Brief description of items	Response options
For vapers		
Intention to Quit E-cigarettes by *Motivation to Stop Scale (MTSS)* [40]	1 item: “Which of the following describes your intention regarding e-cigarette use?”	7 response options, ranging from (1) “I don’t want to stop using e-cigarettes” to (7) “I REALLY want to stop using e-cigarettes and intend to in the next month”
E-cigarette Dependence by *Penn State Electronic Cigarette Dependence Index measures* [41]	6 items (*α*=.51). An example is: “How many times per day do you usually use your electronic cigarette?”	7 response options, ranging from (1) “0‐4 times/day” to (7) “30+ times/day”
For nonvapers		
Future Addiction by adapted *Pierce Susceptibility Questionnaire* [42]	3 items. An example is: “If one of your best friends offered you an e-cigarette, would you smoke it?”	4-point Likert scale, ranging from (1) “Definitely yes” to (4) “Definitely not”
For all participants		
E-cigarette Perceived Harm and Addiction [43]	3 items. An example is: “How likely is someone to become addicted to e-cigarettes/vaping?”	4-point Likert scale, ranging from (1) “Unlikely” to (4) “Likely”
Other Substance Use (cigarettes, marijuana, alcohol) [44]	6 items. An example is: “How many days in the past 30 days have you smoked a cigarette?”	7 response options, ranging from (1) “0 day” to (7) “All 30 days”
Impulse behavior by *Short UPPS-P Impulsive Behavior Scale* [45]	20 items (*α*=0.74‐0.88), based on the following subscales: Negative urgency (4 items), Lack of perseverance (4 items), Lack of premeditation (4 items), Sensation seeking (4 items), Positive urgency (4 items)	4-point Likert scale, ranging from (1) “Strongly agree” to (4) “Strongly disagree.”
Emotional regulation by *Brief Difficulties in Emotion Regulation Scale (DERS-18)* [46]	18 items (*α*=0.77). An example is: “I pay attention to how I feel.”	5-point Likert scale, ranging from (1) “Almost Never” to (5) “Almost Always”

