##### Primary Analyses

For the primary aim of examining differences in psychological and physiological responses between vapers and nonvapers during VR cue exposure with and without social pressure, a mixed-model ANOVA will be conducted. Group (vapers vs nonvapers) will serve as the between-subjects factor, and cue condition (social pressure vs no social pressure) as the within-subjects factor. If the assumptions of normality or homogeneity of variance are violated, nonparametric alternatives such as the aligned rank transform ANOVA [55] will be used to preserve the ability to test interaction effects within the mixed design. Follow-up pairwise comparisons will be conducted with Bonferroni-adjusted *P* values.

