##### Secondary Analyses

For the secondary objective, we will assess associations between multimodal physiological measures and subjective vaping-related outcomes. Correlation and regression analyses will first be conducted to examine pairwise relationships among eye-gaze metrics (eg, total fixations and mean fixation duration), HR, EDA, and subjective measures (eg, craving, dependence scores, and motivation to quit or susceptibility to initiate use). Depending on data distribution, the Pearson or Spearman correlations will be used. Partial correlations or multiple regression models will account for potential covariates such as age, gender, and other substance use.

To further explore multivariate relationships between physiological responses and vaping-related outcomes, exploratory regularized regression analyses will be conducted. Given the pilot sample size, we will use regularized logistic regression with the least absolute shrinkage and selection operator to examine whether aggregated physiological and subjective measures are associated with vaping status (vaper vs nonvaper). Candidate predictors will include summary features derived from eye-gaze behavior (eg, fixation count, proportion of fixation duration on vaping-related cues, and time to first fixation), HRV metrics derived from photoplethysmography signals (including time-domain indices such as root mean square of successive differences and frequency-domain measures such as low-frequency to high-frequency ratio), EDA (eg, mean number of SCRs, mean SCR amplitude, and mean skin conductance level), and relevant subjective responses (eg, craving, presence, and social presence).

Physiological signals will undergo standard preprocessing procedures, including signal quality checks, removal of segments affected by motion artifacts or signal instability, and aggregation into scene-level summary features. Participants will be excluded if more than 15% of their physiological data is missing, and EDA signals will be removed if more than 15% of values are zero or negative, indicating poor sensor contact [56,57]. The regularization parameter will be selected using cross-validation to reduce overfitting [58]. Given the exploratory nature of this analysis and the modest sample size, findings will be interpreted cautiously and used to identify candidate multimodal markers for future confirmatory studies rather than to develop generalizable prediction models.

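### Other-nicotine users stay in both groups on a promise to measure and adjust for that use, but Table 1 lists no pouch item and the primary ANOVA has no such term, so the vaper–nonvaper contrast can be diluted or confounded

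*Protocol article*

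**What the plan says.** Study Population and Study Flow defines vapers by nicotine e-cigarette use, "defined as use on 10 days or more within the past 30 days", and nonvapers as "individuals who report never having used nicotine-containing vapes". Neither definition mentions other nicotine products. The same paragraph says that people who use nicotine in other forms ("eg, cigarettes and nicotine pouches) will not be excluded but will be assessed at baseline so that such exposure can be accounted for analytically".

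The relevant row of Table 1 in Assessments is headed "Other Substance Use (cigarettes, marijuana, alcohol"), with six items. No other row of Table 1 concerns nicotine pouches or any other non-vape nicotine product.

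Primary Analyses specifies: "Group (vapers vs nonvapers) will serve as the between-subjects factor, and cue condition (social pressure vs no social pressure) as the within-subjects factor". The nonparametric fallback and the follow-up comparisons add no covariate. Other substance use enters only under Secondary Analyses: "Partial correlations or multiple regression models will account for potential covariates such as age, gender, and other substance use".

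**The concern.** Someone who smokes or uses pouches daily but has never vaped is an eligible nonvaper, and a vaper may also smoke or use pouches. The article defends this by promising measurement and analytic handling, immediately before it says that the design permits the comparison of vapers with nonvapers. Its own table and its own primary model do not deliver that safeguard for the comparison.

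Two distortions are possible, in opposite directions. Nicotine-using controls who react to vaping cues narrow the group gap. Other nicotine use concentrated among vapers can widen it, so that part of what is read as a marker of vaping is a marker of other nicotine exposure. Among nonvapers, existing nicotine use could also produce a correlation between reactivity and susceptibility. The Background section itself states that nicotine cues draw stronger responses from smokers than from nonsmokers, so some reactivity in smoking controls is plausible on the article's own premise.

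**Working it through.** **1. The promise against the plan**

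| Exposure | Listed in Table 1? | In primary ANOVA? | In secondary models? |
|---|---|---|---|
| Cigarettes | Yes | No | Yes, as a potential covariate |
| Nicotine pouches | No | No | Not possible with the listed measures |

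**2. The article's own figure.** Study Design powers the group × cue condition interaction at f=0.25, r=0.50 ("partial η-squared ≈ 0.06; power=0.80") and arrives at a "minimum required sample of 34 (n=17 per group"). For a 2×2 mixed design with m=2 scenes, λ = f²·N·m/(1−r), on 1 and N−2 df. No alpha is stated; I take 0.05.
- N=32: λ = 0.0625×32×2/0.5 = 8.0, power 0.781.
- N=34: λ = 8.5, power 0.807.
- N=40: λ = 10.0, power 0.869.

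So 34 reproduces as the smallest even N. The sample-size figure is not in error on this point.

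**3. Dilution of the group main effect.** Assumptions, none from the documents: a per-scene gap of 0.8 SD; j of the 20 nonvapers use other nicotine; they show a fraction c of the vaper effect in both scenes. From the documents: r=0.50 and 20 per group. The SD of a two-scene mean is √((1+0.50)/2) = √0.75 = 0.866. The expected gap is 0.8×(1 − c·j/20). Power is for a two-sample t-test on scene means, by simulation, which includes the extra spread in the mixed control group.

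| j of 20 | Gap, c=1 | Power, c=1 | Gap, c=0.5 | Power, c=0.5 |
|---|---|---|---|---|
| 0 | 0.80 | 81% | 0.80 | 81% |
| 2 | 0.72 | about 72% | 0.76 | about 77% |
| 4 | 0.64 | about 60% | 0.72 | about 72% |
| 6 | 0.56 | about 48% | 0.68 | about 67% |

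**4. The interaction.** If nicotine-using controls are shifted equally in both scenes, the shift cancels in the interaction contrast and its expected value does not change. It shrinks only under the further assumption that these controls also share the vapers' difference between scenes. Then f falls to 0.25×(1 − c·j/20). At N=40 and c=1, power goes from 0.869 to 0.792 (j=2, f=0.225) or 0.693 (j=4, f=0.20).

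**5. The opposite direction.** If a share p of vapers also use other nicotine and this adds e SD to their response, the unadjusted gap becomes 0.8 + p·e. With assumed p=4/20 and e=0.5 it is 0.8 + 0.2×0.5 = 0.90 SD. Without the exposure data, the sign of the net bias is unknown.

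**6. Nonvaper correlations.** Assume 4 of 20 nonvapers use nicotine and sit 1 or 1.5 SD higher on both reactivity and susceptibility, with no other association. Unadjusted rejection at the 5% level is about 9% or 21%. Partialling out a measured indicator of that use brings both to about 5%. The adjustment named under Secondary Analyses can therefore work for cigarettes, but not for a product that is not recorded.

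**The case against.** A reader might infer that the primary contrast is diluted. The documents do not support that. Such users are merely not excluded; no prevalence is given, and nothing shows how never-vaping smokers or pouch users would respond to vaping cues and a craving item that asks about vaping. Full reactivity is an upper bound, and dual use among vapers pushes the other way. This stands.

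The power figures in step 3 concern the group main effect, whereas the study is powered on the interaction, where a uniform shift cancels. This also stands as a limit on the size. It does not remove the point, because the first primary hypothesis is that vapers respond more strongly than nonvapers across both scenes.

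A reader might also infer inflated false positives in the susceptibility correlations. For cigarettes the planned covariate adjustment deals with that; only the pouch part remains.

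The absence of other substance use from the LASSO candidates is not a fault: that analysis is exploratory and looks for candidate markers.

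Finally, Table 1 gives brief descriptions in a condensed article, and the full questionnaire and screener are not shown. A pouch item may exist there. But the row names three substances without marking them as examples, and the primary model's factors are stated outright. The mismatch is therefore between printed statements and is not simply detail left to another document.

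**Conclusion.** The point holds as an internal mismatch. The article gives a safeguard as its reason for admitting other-nicotine users; with the listed measures that safeguard cannot be applied to pouches at all, and as specified it is not applied to the primary contrast for cigarettes either. This part rests on no assumption beyond the printed text.

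The consequence is conditional: the contrast can be diluted or confounded. Under the stated assumptions the loss of main-effect power is about 4 points (2 of 20 at half reactivity) to 33 points (6 of 20 at full reactivity), from a starting 81%. Neither the share of such participants nor their reactivity comes from the documents, so these figures show a range and predict nothing. It deserves action now because each participant attends a single session with no follow-up and 7 had been enrolled by March 2026, so an exposure not recorded becomes harder to recover as enrolment proceeds.

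**What to change.** - Add one item to Part 1 of the questionnaire on past-30-day use of nicotine pouches and any other non-vape nicotine. Ask it of participants already enrolled, or flag them as missing it. If the full questionnaire already has such an item, correct Table 1 instead.
- Keep the group comparison of the registered protocol as primary. Add a prespecified sensitivity analysis of the primary contrast that either excludes participants with past-30-day non-vape nicotine use from both groups or adjusts for that use; choose one in advance.
- Include the new item in the other-substance-use covariate of the secondary analyses, above all for the susceptibility correlations among nonvapers.

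I would not make restriction of the nonvapers alone the primary analysis. It leaves dual users among the vapers, so the contrast becomes less specific to vaping, and dropping 4 or 6 of 20 nonvapers leaves 16 or 14, below the article's minimum of 17 per group.

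The cost is one extra item, a smaller sample in the sensitivity analysis if exclusion is chosen, and incomplete data for the first participants.

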### Aims

#### Overview

The overall goal of this study is to evaluate the feasibility of VR-based psychophysiological assessment methods as an early detection and risk prediction tool for nicotine addiction. This paper presents a mixed methods experimental study protocol designed to examine how psychophysiological responses to vaping cues in VR differ among young adults based on their nicotine vaping status and intentions. The study integrates psychological, physiological, and qualitative measures across 2 bespoke VR cue exposure scenes. Participants include two groups: (1) young adults who currently vape (vapers), for assessment of nicotine dependence and quit intentions; and (2) individuals who have never vaped (nonvapers), for evaluation of susceptibility to initiation.

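### Other nicotine use is to be assessed and accounted for, but the listed baseline measure omits nicotine pouches and the primary ANOVA makes no provision for other nicotine use

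*Protocol article*

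**What the plan says.** **Eligibility (Study Population and Study Flow).** The nonvaper group consists of "individuals who report never having used nicotine-containing vapes". The next sentence covers both groups and says of people taking nicotine by another route that they "will not be excluded but will be assessed at baseline so that such exposure can be accounted for analytically"; its two examples are cigarettes and pouches. A current smoker or pouch user who has never used a nicotine vape can therefore be a nonvaper, and a vaper may also smoke or use pouches.

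**Baseline measure (Assessments, Table 1).** The relevant row is headed "Other Substance Use (cigarettes, marijuana, alcohol"). It has 6 items, and the one shown asks on how many of the past 30 days the participant smoked a cigarette. The list of substances is not introduced as examples, and no other row covers pouches.

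**Primary model (Primary Analyses).** The between-subjects part is given as "Group (vapers vs nonvapers) will serve as the between-subjects factor". The only other factor is cue condition, within subjects. No covariate, stratification or sensitivity analysis for other nicotine use is named.

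**Secondary models (Secondary Analyses).** "Partial correlations or multiple regression models will account for potential covariates such as age, gender, and other substance use".

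**Wording of the aims (Overview).** The comparison group is described as "individuals who have never vaped (nonvapers"), which is narrower than the eligibility rule. The Primary Aim uses the same shorter description.

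**The concern.** The article names pouches as an exposure it will assess, then lists a baseline measure without them. It also says that other nicotine use can be handled in the analysis, yet the analysis of the primary aim does not handle it.

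The Background section takes as its premise that smokers respond more strongly than nonsmokers to nicotine-related cues. On that premise, nonvapers who use nicotine in another form may react more like vapers, which would shrink the group contrast. Other nicotine use among vapers could instead widen it. In either case the primary comparison mixes vaping status with other nicotine exposure.

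The eligibility section excludes several other substances to sharpen the separation between groups, but nicotine from other sources stays in without any protection in the primary analysis. If pouch use is not recorded at the visit, it cannot be adjusted for later.

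**Working it through.** **1. Passages side by side**

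| Exposure | Allowed in both groups | In the listed baseline measure | In the primary ANOVA | In the secondary models |
|---|---|---|---|---|
| Cigarettes | Yes, named | Yes | No | Yes, as other substance use |
| Nicotine pouches | Yes, named | No | No | Not possible from the listed items |

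**2. The plan's own sample size**

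Inputs from Study Design: f = 0.25, correlation between cue conditions ρ = 0.50, m = 2 conditions, 2 groups, power 0.80, minimum N = 34, planned N = 40. Alpha is not stated; 0.05 is assumed here.

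For the group × cue interaction, λ = f²·N·m/(1−ρ), with 1 and N−2 degrees of freedom.

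- N = 34: λ = 0.0625 × 34 × 2/0.5 = 8.5, power 0.807.
- N = 32: λ = 0.0625 × 32 × 2/0.5 = 8.0, power 0.781.

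The minimum of 34 is reproduced, so the sample size arithmetic is not at fault. At N = 40, λ = 10.0 and power is 0.869.

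**3. Worst-case dilution**

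Suppose a share p of nonvapers responds exactly as vapers do. The group contrast, and with it the interaction, is multiplied by (1−p), so f becomes 0.25(1−p). The documents give no value for p, so it is an assumption and a range is shown. At N = 40, λ = f² × 160 for the interaction. For the group main effect, λ = f²·N·m/(1+ρ) = f² × 80/1.5.

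| p | f | λ, interaction | Power, interaction | Power, group main effect |
|---|---|---|---|---|
| 0 | 0.250 | 10.0 | 0.869 | 0.429 |
| 10% (2 of 20) | 0.225 | 8.1 | 0.792 | 0.360 |
| 20% (4 of 20) | 0.200 | 6.4 | 0.693 | 0.296 |
| 30% (6 of 20) | 0.175 | 4.9 | 0.578 | 0.238 |

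If affected nonvapers respond only half as strongly, the multiplier is (1−p/2). Interaction power is then 0.833, 0.792 and 0.745 for p = 10%, 20% and 30%.

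**4. What the possible remedies cost**

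- *Excluding nonvapers.* Removing 2, 4 or 6 nonvapers leaves 20 against 18, 16 or 14. The balanced-equivalent N is 4·n₁·n₂/(n₁+n₂) = 37.9, 35.6 or 32.9. With the undiluted f = 0.25, interaction power is about 0.85, 0.83 and 0.79.
- *Adding a covariate.* A between-subject main-effect term does not adjust the group × cue interaction; a covariate × cue term is also needed. If the covariate is unrelated to group, only 1 error degree of freedom is lost (0.868 against 0.869). If 10 of 20 vapers but 2 of 20 nonvapers used other nicotine (an assumption), the correlation with group is 0.4 × 0.5/√(0.3 × 0.7) = 0.44. Then λ = 10 × (1 − 0.19) = 8.1, and power is about 0.79 if the covariate explains no variance.

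**The case against.** **The text promises less than one might infer.** A reader might infer that adjustment in the primary model is promised. The article says only that other nicotine exposure can be accounted for analytically, and the secondary models do account for other substance use. This stands: the fault is a gap between a stated intention and the primary analysis, not a broken promise about a particular model.

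**Cigarettes are measured.** A reader might infer that no correction is possible with the listed measures. That is wrong, because Table 1 contains a past-30-day cigarette item. The problem is confined to pouches and other unlisted forms. The susceptibility analysis is likewise secondary and can be adjusted for the substances that are listed.

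**The article is condensed.** The full questionnaire and screener are not shown, so it is not established that pouch use goes unrecorded; it is only not listed. Covariates are also often left to an analysis plan. This softens the point but does not remove it. The article itself names pouches as an exposure and then lists the measure without them. The screener is described only as determining eligibility, for which other nicotine use is not a criterion.

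**Dilution is not certain.** Other-nicotine users may be in both groups, so the direction of bias depends on an unknown imbalance. Full vaper-like response is an extreme assumption, because the craving item and the gaze regions are specific to vaping. This stands, and the power figures are therefore upper bounds on the loss for a given p.

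**The nonvaper definitions.** A reader might infer two conflicting populations. The operational rule in the eligibility section is clear, and the aims read as shorthand for it. This is a wording mismatch.

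**Conclusion.** The concern holds in a limited form. Two statements in the article do not fit together: other nicotine use, with pouches named, is to be assessed so that it can be accounted for, yet the listed measure omits pouches and the primary analysis has neither a term nor a sensitivity analysis for other nicotine. The primary vaper-nonvaper contrast is thus open to confounding, with dilution the more likely direction if nicotine-using nonvapers enrol.

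The size cannot be fixed from the documents. In the worst case, interaction power at N = 40 drops from 0.87 to 0.79, 0.69 or 0.58 for p = 10%, 20% or 30%; with half-strength response it stays between 0.83 and 0.75. These figures rest on alpha = 0.05, the plan's f and ρ, and an assumed p. The allowance from 34 to 40 participants is already meant for data loss, so it is not a free reserve against dilution.

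This should be corrected now, because pouch use that is not recorded cannot be adjusted for at the analysis stage.

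**What to change.** 1. Add a past-30-day item on nicotine pouches and other non-e-cigarette nicotine to Part 1 of the questionnaire. Ask the participants already enrolled retrospectively; Ethical Considerations says that identities stay linked to study data through coded IDs, so this is feasible.
2. Keep the primary ANOVA as stated. Prespecify a sensitivity analysis that repeats it (a) after excluding nonvapers with any current nicotine use and (b) after excluding other-nicotine users from both groups, so that the contrast is symmetric.
3. If a covariate model is also reported, include other-nicotine use and its interaction with cue condition, and label the model supportive.
4. Align the never-vaped wording in the Overview and Primary Aim with the operational definition in Study Population and Study Flow. Do not change the screener mid-study, since that would mix two nonvaper definitions.

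**Cost.** One questionnaire item, a few sentences of analysis text, somewhat smaller sensitivity samples, and retrospective recall for those already enrolled (7 as of March 2026).
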